**Methods:**

Seventy-five participants will take part. The trial will include in-home and supervised hospital experimental training compared to a non-active control group in order to estimate the actual effect of the proposal against the benefits due exclusively to the surgical procedure. Interventions last 4 weeks prior to surgery, and the follow-up will be at 2w, 6w, and 1y following the operation. The primary outcomes are in agreement with the goals: self-reported functionality in terms of KOOS and overall balance in terms of the Berg Balance Scale. The secondary outcomes will include the measurements of static and dynamic balance abilities, pain, function, and quality of life.

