##### EuroQoL-5D

This is a questionnaire administered to measure the health-related quality of life. The descriptive system contains 5 dimensions of health [27]. It is important to note that preoperative anxiety is being assessed with item number 5 of this test.

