#### Outcome assessment

The baseline assessments will be carried out by a physiotherapist blinded to the interventions, following the signing of an informed consent form and prior to the start of the physiotherapy sessions. The proposed time for the outcome evaluation is in the preoperative period (baseline, between 8 and 4 weeks), before (1 week) and after (2 weeks) the surgical procedure, after the postoperative intervention (6 weeks) and 12 months follow-ups. Details are given in Table 2.

**Table 2 Tab2:** Detail of variables and times for evaluation of outcomes

Time point	Enrolment	BL	BP	AP	AI	12 m
Eligibility screen	x					
Informed consent	x					
Randomization	x					
Assessments						
Demographic and biomedical	x					
Primary						
Self-reported functionality	KOOS	x	x	x	x	x
Balance (overall)	Berg Balance Scale	x	x	x	x	x
Secondary						
Function	ROM (flexion)	x	x	x	x	x
	ROM (extension)	x	x	x	x	x
	Strength	x	x	x	x	x
Balance (dynamic)	Timed Up & Go	x	x	x	x	x
(static)	One-leg Stand	x	x		x	x
(stability)	Functional Reach	x	x	x	x	x
Quality of Life	EuroQoL	x			x	x
Anxiety	EuroQoL(5D)	x	x		x	
Cost-effectiveness						
	Qaly					x
Patient expectations						
		x			x	x
Interventions		BL	BP	AP	AI	12 m
Non-active comparator				x------x		
In-hospital preoperative		x------x		x------x		
In-home preoperative		x------x		x------x		

*BL* Baseline, *BP* Before procedure, *AP* After procedure, *AI* After intervention, *KOOS* Knee Injury Osteoartritis Outcome Score, *ROM* Range of Movement in degrees, *Qaly* Quality adjusted life year

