#### Economic evaluation

An economic analysis will be carried out to evaluate the cost-effectiveness of the experimental proposals versus the non-active comparator proposal. This will take into consideration all costs that are potentially related to each intervention, to the resources related to the training of the participant in the hospital, or in the case of performing the intervention at home, related to education and the time invested in monitoring the participant in order to ensure the compliance with the treatment. Appropriate unit costs will be allocated according to data from the national health system, including not only the time spent by physiotherapists but also by physicians [32].

The measure of effectiveness will be based on the results of the EuroQoL-5D, which will be used to estimate Quality Adjusted Life Years (QALY) estimated with the Spanish intervention rate associated with the time trade-off method. The analysis will be based on the mean overall cost and mean overall effect of each intervention. If a technique is less costly and more effective it will be deduced that it is cost-effective and therefore the one that will best optimize the use of resources. The acceptability curve will be plotted for the estimation of uncertainties. Finally a sensitivity analysis will allow to know the robustness.

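### The EQ-5D that supplies the QALYs is not taken just before or 2 weeks after surgery, so the between-arm QALY difference depends on an early course that nobody measures

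*Protocol article*

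**What the plan says.** In the Protocol article, Economic evaluation, the effect side of the cost-effectiveness analysis is fixed: "The measure of effectiveness will be based on the results of the EuroQoL-5D", converted to QALYs with Spanish time trade-off values.

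The visit times are in Outcome assessment. Baseline is 8 to 4 weeks before surgery, and the later visits are "before (1 week) and after (2 weeks) the surgical procedure, after the postoperative intervention (6 weeks) and 12 months follow-ups". Table 2 labels them BL, BP, AP, AI and 12 m. The row "Quality of Life EuroQoL" is marked at BL, AI and 12 m, and its BP and AP cells are blank. KOOS and the Berg Balance Scale are marked at all five visits.

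A separate anxiety row in Table 2, also drawn from the EuroQoL, is marked at BL, BP and AI. The EuroQoL-5D section explains that "preoperative anxiety is being assessed with item number 5 of this test", so this row is one item and not the full questionnaire.

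On the timing of the treatment contrast, the Abstract states "Interventions last 4 weeks prior to surgery". Table 1 and the Interventions section give all three groups the same postoperative programme.

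**The concern.** The arms differ only in what happens between baseline and surgery. The two visits closest to that difference, BP at or near the end of training and AP 2 weeks after the operation, carry no utility measurement. One EQ-5D item at BP cannot be turned into a utility.

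The Background says that a preoperative programme can improve early results and that the evidence on later effects is inconclusive, so an early effect that fades is a realistic possibility. By 6 weeks all arms have also had the common 12-session programme. If the effect does fade, the training costs are counted in full while part or all of the utility gain is not. Whether benefits justify costs is a stated aim in the Abstract, the Background and the Discussion, and the incremental QALY is half of that answer.

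**Working it through.** The article gives no QALY figure to reproduce. The check asks how far three EQ-5D visits can depart from five, for different courses of the between-arm utility difference.

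**Inputs from the Protocol article.** Baseline is at −L weeks with L from 4 to 8, BP at −1, AP at +2, AI at +6 and the last visit at +52 weeks (Outcome assessment; the Abstract counts follow-up from the operation). The gap between the first two utilities is L + 6, so 4 + 6 = 10 to 8 + 6 = 14 weeks.

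**Assumptions not in the article.** QALYs are the straight-line (trapezoid) area under the utilities. The between-arm difference is zero at baseline. The profiles are illustrative, in units of a utility gain d.

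**Formula.** Write u for the between-arm utility difference at a visit.

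- Five-visit area up to 6 weeks: (L − 1)/2 × u_BP + 3/2 × (u_BP + u_AP) + 4/2 × (u_AP + u_AI).
- Three-visit area up to 6 weeks: (L + 6)/2 × u_AI.
- From 6 to 52 weeks the two are identical: 46/2 × (u_AI + u_12m).
- Subtracting: missed weeks = (L + 2)/2 × (u_BP − u_AI) + 3.5 × u_AP.

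A positive result is an undercount and a negative one an overcount. The first term is negative whenever the gain at 6 weeks exceeds the gain at BP, so the sign is not fixed.

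**Example.** With L = 8 and half the gain left at 6 weeks: 5 × (1 − 0.5) + 3.5 × 1 = 6 weeks missed. The five-visit area with nothing left at 12 months is 3.5 + 3 + 3 + 11.5 = 21 weeks, and 6/21 = 29%.

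**Results.** Areas are in weeks × d, shown for L = 8 then L = 4. The percentage is the error divided by the five-visit area.

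| Difference at BL, BP, AP, AI, 12 m | Five visits | Three visits | Error |
|---|---|---|---|
| 0, 1, 1, 0, 0 | 8.5; 6.5 | 0; 0 | 100% missed |
| 0, 1, 1, 0.5, 0 | 21; 19 | 15; 14 | 29%; 26% missed |
| 0, 1, 1, 0.5, 0.25 | 26.75; 24.75 | 20.75; 19.75 | 22%; 20% missed |
| 0, 1, 1, 1, 0 | 33.5; 31.5 | 30; 28 | 10%; 11% missed |
| 0, 1, 1, 1, 1 | 56.5; 54.5 | 53; 51 | 6% missed |
| 0, 0.5, 0.5, 1, 1 | 52.25; 51.25 | 53; 51 | 1.4% over; 0.5% missed |
| 0, 0.25, 0.25, 1, 1 | 50.125; 49.625 | 53; 51 | 6%; 3% over |
| 0, 0, 0, 1, 1 | 48; 48 | 53; 51 | 10%; 6% over |

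The percentages do not depend on d. For an illustrative d = 0.10, the absolute error is missed weeks × 0.10/52:

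- First row: 0.0163 to 0.0125 QALY missed.
- Half-remaining rows: 0.0115 to 0.0096 QALY missed.
- Rows with the full gain at BP, AP and 6 weeks: 3.5 × 0.10/52 = 0.0067 QALY missed.
- Last row: 5 × 0.10/52 = 0.0096 to 3 × 0.10/52 = 0.0058 QALY overcounted.

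**The case against.** The strongest objection concerns direction. A reader might infer that the schedule biases the economic result against both training arms, because their costs are complete and their early gains are not. The article does not support that. It holds when the gain is already large at BP and AP, but a gain that builds up after surgery and lasts is overcounted. Nothing in the article says which course to expect. This objection stands in full and limits the claim.

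Second, the Data analysis section gives particular attention to 6 weeks and 1 year, and the EQ-5D is taken at both. A benefit that is complete by BP and still full at 6 weeks is 89–94% captured. This also stands, although the same section says that every time point is of interest.

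Third, the article does not say that QALYs will be a straight-line area. That is correct, and the omission is no fault in an article. But any method confined to the scheduled visits has no utility at BP or AP.

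Fourth, KOOS is taken at all five visits, and a sensitivity analysis is planned. KOOS will show an early clinical difference but is not a utility. The sensitivity analysis can vary assumptions about the missing values but cannot recover them. This answers the point only in part.

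Fifth, the amounts are small beside sampling error. With an assumed QALY standard deviation of 0.10 to 0.20 and 20 completers per arm, the standard error of a difference is SD × √(2/20), about 0.03 to 0.06. Cost-effectiveness is listed under other outcomes, and an early gain shared by both training arms would largely cancel between home and hospital. These arguments lower the severity. They do not remove a systematic error in the planned comparison with the non-active arm, and imprecision is no reason to leave an avoidable error in the point estimate.

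**Conclusion.** The point holds as a measurement gap and not as a bias of known sign. No utility is measured for 10 to 14 weeks around the only period in which treatment differs. Across the profiles examined, the error in the between-arm QALY runs from missing all of it (early gain gone by 6 weeks), through 20–29% (half remaining), 10–11% (full at 6 weeks, gone by 12 months) and about 6% (fully sustained), to overcounting by 6–10% (gain appearing only by 6 weeks and lasting). An early, fading benefit would be undercounted against costs counted in full, and the data as scheduled cannot show whether that happened.

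These figures rest on the straight-line area, a zero difference at baseline and the assumed profiles. The absolute QALY amounts rest in addition on an illustrative d. The severity is modest: the primary outcomes are untouched, but a prominent aim of the trial is affected and the remedy is cheap.

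**What to change.** In Table 2, mark the full EQ-5D at BP and AP as well as at BL, AI and 12 m. In Economic evaluation, state that QALYs are the area under all five utilities, using each participant's actual visit dates.

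The Discussion puts recruitment from March 2017 to an expected end in June 2018, so some participants may already have passed these visits when a change takes effect. For them, treat the BP and AP utilities as missing and use the sensitivity analysis already planned to show the incremental QALY over a range of early profiles, including ones in which the three-visit schedule overcounts.

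The cost is a minute or two of patient time at two visits that already take place, a short amendment, and incomplete five-point data for participants enrolled earlier.

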### Data analysis

The implementation of protocols will be presented with descriptive statistics. In an exploratory way, the drop-out ratios will be estimated and the survival analyses will be used [29]. This aspect will also be taken into account throughout the follow-up and registering when drop-outs occur. The incidence of adverse effects at 6 weeks will be evaluated, which will be categorized according to whether they are considered to be definitive, probable or possibly related to the interventions.

It is hypothesized that the experimental groups will have enhanced balance abilities, which may also have a direct impact on functionality in the short and mid-term. All temporal instants are of interest, although particular attention will be paid to the early postoperative effects (6w) and maintenance of potential mid-term benefits (1y).

The data analysis will include the sample descriptors, a comparison of the baseline condition with the t tests that will be parametric or not depending on the results of the tests of Wilcoxon and Shapiro-Wilk, and a comparison of the progress due to the results of the intervention with an ANOVA analysis of repeated measures, looking for interactions initially as a function of time, group, and time per group. In case of baseline differences between the participants, an ANCOVA analysis will be conducted instead, in which the data will be adjusted to the baseline scores. Analyses will be performed for primary and secondary outcomes. Post-hoc analyses will be performed accordingly. The significance levels will be set at 95%.

A qualitative analysis will be carried out in which it will be estimated if the obtained progressions measured as the mean values of the difference between the basal and final values for each variable at each time point reach the minimum established according to the psychometric properties referring to the minimum clinical importance difference or minimum detectable change with a CI of 95%, if they are available in the literature. If they had been reported by different studies, it would be based on the suggested minimum value.

A post-hoc power analysis and an estimate of the effect size will be implemented with the tool G*Power [20], based on Cohen’s *d* and considering a low, medium or high effect as a function of the result [30].

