#### In-hospital supervised preoperative intervention (PRE_ EXP1)

Different exercises are proposed and developed over the course of the 12 sessions on alternate days, divided in 4 weeks of training. On the one hand the intervention includes a standard program of rehabilitation with strengthening exercises. In addition, each session includes a total of 4 to 5 balance and proprioceptive exercises performed over a period of 20 min. The training has been based on the Fitzgerald principles to train proprioception, on previous of our works, and on clinical experience [21, 23]. The first 2 weeks are oriented to enhance balance and proprioception with the side, treadmill, cross, and tandem walk exercises. These exercises are excluded in weeks 2 and 3 and multiple changes of direction, foam activities and balance work with the Bohler plate are performed instead. Also 5 min training of weight bearing and testing the limits of stability are performed during the last 4 sessions. Progression in the exercises is implemented as tolerated, always trying to avoid fatigue. The physiotherapist is responsible for recording attendance at rehabilitation sessions.

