#### In-home preoperative intervention (PRE_EXP2)

The in-home exercise program is essentially based on the same principles than PRE_EXP1, but adapted so it can be conducted at home. The first day is an education with the explanation of the exercises. The training is carried out in the hospital and is supervised by the physiotherapist. The participant is asked to repeat the exercises, and possible doubts are resolved. The intervention consists of a phase with exercises to strengthen the main musculature of the lower limb, and a second phase of balance and proprioceptive work. The muscular enhancement exercises are isometric quadriceps in extension, elevations of the lower limb with knee in extension, ankle in dorsal flexion, and slight hip flexion combined with abduction and adduction. Additionally, the middle gluteal and open chain quadriceps are also performed. Each set of exercises is performed in 4 series consisting of 10 repetitions with a rest of 90 s between each series. The proprioception exercises consisted of tandem position and walking, single-leg position, and treadmill walking. Each exercise has to be performed for 2–4 min. And the participants were asked to do so safely, for instance in a hallway or in front of a table or chair, to avoid falls. After session 6, the participant is appointed for a reminder and verification of exercises, as well as possible corrections in the implementation of the intervention. The participant is requested to register the number of sessions performed in a calendar. The physiotherapist phones the participants on a weekly basis, in order to check both the compliance of the program and the calendar fulfillment.

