#### Non-active preoperative intervention (PRE_NA)

In order to evaluate the true effect produced by the interventions, and to determine whether the postoperative results obtained are due to the appropriateness of the proposals, a non-active control group (third arm) was added.

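### Adverse effects are classed only by degree of relation to the interventions; this does not fit the non-active arm before surgery, where contact also differs by arm, so preoperative harms are open to bias

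*Protocol article*

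**What the plan says.** Harms are covered in Data analysis, which first fixes the time point: "The incidence of adverse effects at 6 weeks will be evaluated". Events are then sorted by a single rule: "which will be categorized according to whether they are considered to be definitive, probable or possibly related to the interventions". The sentence gives no class for unrelated events. It does not say when the window opens or who judges relatedness.

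The arms differ by design only before surgery. Table 1 and the intervention rows of Table 2 give the control arm nothing in that phase; the section on the non-active intervention says only that "a non-active control group (third arm) was added", its purpose being to isolate the true effect of the training. After surgery all three arms follow the same programme (Interventions).

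Preoperative contact by arm:

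- **Hospital:** "Different exercises are proposed and developed over the course of the 12 sessions on alternate days, divided in 4 weeks of training". The stated record is attendance: "The physiotherapist is responsible for recording attendance at rehabilitation sessions".
- **Home:** one supervised education day, one check after session 6, and weekly calls "in order to check both the compliance of the program and the calendar fulfillment". Participants are told to exercise safely, "for instance in a hallway or in front of a table or chair, to avoid falls".
- **Control:** no preoperative contact is described other than the assessments that all arms share.

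The shared assessments are at baseline (8 to 4 weeks before surgery), 1 week before surgery (BP), 2 weeks after (AP), 6 weeks after (AI) and 12 months (Outcome assessment, Table 2). Blinding and randomization puts a blinded physiotherapist in charge of outcome assessment.

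**The concern.** The classification presupposes an intervention to which an event can be related. In the control arm before surgery there is none, so a fall or a flare of knee pain in that period has no class. In either training arm the same event, with the same background cause, can be called possibly related. A table built on these classes would charge background events to the training arms and have no place for them in the control arm.

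Separately, the more often a participant is seen or phoned, the more chances there are for an event to come to light. The three arms differ widely in this, and the home arm is the one in which the protocol itself mentions falls.

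The trial asks whether home training can take the place of supervised training at lower cost and whether the proposal suits clinical practice. A reader will look at the harm counts alongside those conclusions. Attribution bias would tend to make training look worse than control. Ascertainment bias could make home training look safer than hospital training, if events surface at contacts.

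**Working it through.** The protocol gives no event rate and no figure for harms, so there is no stated number to reproduce. The check counts contacts and then shows how far identical true risk can drift apart in the counts. Every rate and capture proportion below is an assumption.

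**1. Scheduled preoperative contacts beyond the shared assessments**

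| Arm | Contacts | Total |
|---|---|---|
| Hospital | 12 sessions | 12 |
| Home | 1 education day + 1 check + about 4 weekly calls (4-week programme) | about 6 |
| Control | none described | 0 |

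Adding the two shared preoperative assessments (baseline and BP) gives about 14, 8 and 2.

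**2. Attribution**

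With 25 per arm (75 in 3 equal groups) and background risk p, the expected background events per arm are 25 × p:

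- p = 5%: 25 × 0.05 = 1.25
- p = 10%: 25 × 0.10 = 2.5

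If a proportion q of these is called possibly related in a training arm, that arm shows 25 × p × q related events. The control arm can show no preoperative related event, whatever q is. At p = 10% the spurious gap runs from 0 (q = 0) to 2.5 events (q = 1). This applies to a table of related events; an all-cause table would not have the problem.

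**3. Ascertainment**

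Expected recorded events = 25 × p × c, where c is the proportion of events captured, with p equal in all arms:

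| p | c (hospital / home / control) | Expected recorded events |
|---|---|---|
| 10% | 90% / 70% / 50% | 2.25 / 1.75 / 1.25 |
| 10% | 90% / 50% / 20% | 2.25 / 1.25 / 0.50 |
| 10% | 90% / 90% / 90% | 2.25 / 2.25 / 2.25 |
| 20% | 90% / 50% / 20% | 4.50 / 2.50 / 1.00 |

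Only equal capture returns equal counts.

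**4. Precision**

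Even without bias the data say little. With 0 events in n participants the one-sided 95% upper bound is 1 − 0.05^(1/n): 11.3% for n = 25 and 13.9% for n = 20. Fisher's exact test at 25 per arm has power of about 20% for assumed rates of 5% v 20%, and about 30% for 10% v 30%. One or two missed or misattributed events can therefore change how the table reads.

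**5. Intervals between shared visits**

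Baseline to BP: 4 − 1 = 3 to 8 − 1 = 7 weeks. BP to AP: 1 + 2 = 3 weeks. AP to AI: 6 − 2 = 4 weeks. A question put at each shared visit would need recall of at most 7 weeks up to AI.

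**The case against.** The strongest reply is that this is one condensed sentence in a journal article. How events are elicited, by whom and on what form is commonly left to the full protocol, so its absence here is no finding. That stands, and the point does not rest on the lack of an adverse-event row in Table 2. It rests on the classification that the article does state.

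Several stronger readings are tempting, and the text does not support them:

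- *The control arm will have no preoperative harm count.* The sentence speaks of the incidence of adverse effects and then of categorising them. It does not say that only related events count or that control events are dropped, and control participants are seen 1 week before surgery.
- *The arms cannot be compared.* Both training arms have a preoperative intervention and the same classes apply to both. They can be compared, with bias and low precision.
- *Unblinded staff will decide relatedness.* The text does not say who decides it, and the outcome assessor is blinded.
- *The home calls leave harms out while the hospital sessions pick them up.* The calls' stated purpose is compliance and the calendar, but no question is excluded. The hospital sessions are likewise said only to record attendance. The contact counts measure opportunity to detect an event, not a stated practice of asking.
- *Events must be recalled over 10 to 14 weeks.* This would hold only if nobody were asked before week 6. The shared visits before and after surgery make that unwarranted.
- *Harms stop too early because benefit is followed to 1 year.* The 6-week point coincides with the end of the shared postoperative programme and is defensible.

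It is also fair to say that unequal contact is inherent in comparing supervised, home and no training, that no between-arm test of harms is planned, and that Reproducibility of the interventions says procedures were pilot tested for safety among other things. None of this supplies a class for an unrelated event or makes ascertainment equal.

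**Conclusion.** The point holds in a limited form. The stated classes do not fit the non-active control before surgery, and scheduled preoperative contact is 12, about 6 and 0. Any between-arm reading of preoperative harms is therefore open to attribution and ascertainment bias.

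The absolute size is small: with assumed background risks of 5% to 10%, about 1.3 to 2.5 events per arm. Because the counts are so low, a shift of one or two events is enough to alter the impression given. The bias figures depend on assumed event rates and capture proportions. The mismatch of classes and the contact counts do not, apart from reading weekly calls over 4 weeks as about 4.

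This does not touch the efficacy analysis. It is an inexpensive improvement to how harms are counted and described, and it should be made.

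**What to change.** Replace the harm sentence in Data analysis with wording such as: *All adverse events and falls from randomisation are counted in all three arms whatever their cause, and are tabulated by arm, before and after surgery separately. Relatedness (definite, probable, possible, unrelated) is a secondary description.*

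Have the blinded assessor put the same fixed question on falls and adverse events to every participant at the existing BP, AP and AI visits. Base the between-arm description on those answers only. Events that surface at sessions or calls can still be recorded, but should be listed apart. Because an answer may reveal the allocation, ask the question after the outcome measures at that visit have been scored.

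Cost: a short amendment and one question at visits that already take place. It adds no visit or staff and changes no treatment. The downsides are slightly more recording and higher reported counts.

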## Method

### Design and ethics

This is a 3-arm randomized trial, which is carried out prospectively at Hospital Universitario y Politécnico La Fe of Valencia, Spain. The trial has been designed in accordance with the guidelines proposed in the Helsinki Declaration, was approved by the Ethical Committee for Clinical Research and by the Scientific Committee of the mentioned hospital, and was prospectively registered in April 4, 2017 (clinicaltrials.gov identifier NCT-03100890).

Potential participants must give express consent for the use of data for exclusively scientific and research purposes. The data are anonymized from the origin, with initials and numerical identifiers for the electronic bases. The data will be extracted by the evaluators and managed exclusively by the principal investigator of this project, who will be the only one with access to the complete database. The database will be kept in the Physiotherapy Department of the University of Valencia, subject to the center’s security protocols.

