### Sample size

A priori sample size estimation was made with the tool G*Power3.1 [20]. One-way ANOVA power analysis with three groups was based on the results of previous works [21]. The analysis considered that the groups receiving preoperative intervention will reach a score on the primary outcome the Berg Balance Scale of 53, this score being 5 points above that of the non-intervention group, with a reasonable standard deviation of 4.5 points, and with α = 0.05. The trial must consist of groups of 20 participants in order to achieve *d* > 0.8 and *f*
^2^ > 0.5. Predicting over 20% of sample loss, a total of 75 participants will be divided into 3 equal groups. Once data are collected, a post-hoc analysis will determine if the sample provided sufficient power to the trial.

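### The baseline comparison uses a two-group test in a three-arm trial and lists Wilcoxon as a distribution check, and its result decides whether the main model is ANCOVA

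*Protocol article*

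**What the plan says.** The protocol article, under Design and ethics, states "This is a 3-arm randomized trial". Under Data analysis, the baseline condition is compared by "the t tests that will be parametric or not depending on the results of the tests of Wilcoxon and Shapiro-Wilk". No three-group test is named for baseline, no pairs of arms are specified and no adjustment is mentioned.

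The following sentence gives the result a use: "In case of baseline differences between the participants, an ANCOVA analysis will be conducted instead", with adjustment to the baseline scores. The model being replaced is the repeated-measures ANOVA with time, group and their interaction, planned for primary and secondary outcomes. The text does not define what counts as a baseline difference.

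The error level is given as "The significance levels will be set at 95" per cent, which I read as alpha = 0.05. That agrees with the Sample size section: "with a reasonable standard deviation of 4.5 points, and with α = 0.05".

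**The concern.** The sentence contains two errors.

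1. **Wrong number of groups.** A t test, or its rank counterpart, compares two groups. With three arms it can only be run on pairs, and the plan leaves open which pairs and at what level. The document uses three-group methods elsewhere: the sample size rests on a one-way ANOVA with three groups, and the outcomes are analysed by repeated-measures ANOVA.
2. **Wrong kind of check.** Wilcoxon is a rank test of location. It is listed beside Shapiro-Wilk as evidence for choosing parametric or non-parametric testing, but it does not examine shape. The rule also does not say what to do when the two disagree.

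In most trials a loosely worded baseline test affects only p-values in a table. Here it also selects the main model. A false-positive rate above 5% at baseline therefore means that chance switches the analysis more often, and two analysts who read the sentence differently could arrive at different main models.

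**Working it through.** **Inputs.** Three arms (Design and ethics). Berg means 53, 53 and 48, SD 4.5, alpha 0.05, 20 per group, 20% loss, 75 in total (Sample size). Two-sided testing is assumed, because the article does not state sidedness.

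**The plan's own figure.** The article gives no error rate for the baseline tests, so the figure to reproduce is the sample size, which fixes the number per arm.
- Grand mean = (53 + 53 + 48)/3 = 51.33.
- SD of the means = √[(1.667² + 1.667² + 3.333²)/3] = √5.556 = 2.357.
- f = 2.357/4.5 = 0.524.
- Three-group ANOVA power is 0.952 at 20 per group and 0.941 at 19. The target power is not stated; 0.95 is assumed because it returns 20.
- Total = 3 × 20 = 60, and 60/(1 − 0.20) = 75, or 25 per arm.

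Both 20 and 75 reproduce. Nothing in this point changes them.

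**False baseline differences per variable.** The arms are randomised, so any baseline difference is chance and the null holds. Treating the pairwise tests as independent gives upper bounds:
- three pairs: 1 − 0.95³ = 14.3%;
- two pairs: 1 − 0.95² = 9.75%.

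The comparisons share arms and are not independent, so the actual rates are lower. From 200,000 simulated trials of normal data with 25 per arm:

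| How the baseline test is run | Chance of at least one false flag | Ratio to 5% |
|---|---|---|
| One three-group ANOVA | 5.0% | 1.0 |
| Two active-versus-control t tests, unadjusted | 9.0% | 1.8 |
| All three t tests, unadjusted | 12.1% | 2.4 |
| All three t tests, Bonferroni | 4.4% | 0.9 |

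As a check, the studentized range distribution for three means at the pooled t cut-off (72 df) gives 12.1%. With 20 per arm the three-pair figure is 12.3%.

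**Both primary outcomes.** If KOOS ADL and Berg are each screened by all three unadjusted pairs, the chance that at least one is flagged is 23% at correlation 0 and 20% at correlation 0.7. The documents give no correlation, so this range is an assumption.

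**Wilcoxon as a distribution check.** In 4,000 simulated pairs of 25, with exponential data and identical arms, Wilcoxon is significant in 4.4%, while Shapiro-Wilk detects the skew in at least one arm in 99.3%. On normal data with identical arms, Wilcoxon is significant in 5.2%. Its rate is thus about the same for strongly skewed and normal data, so it carries no information about shape.

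**The case against.** The strongest reply is that the pairing is inferred. The article does not say that the tests are pairwise, that there are three of them, or that they are unadjusted, and such details are commonly left to a full protocol or SAP. This stands. A reader might infer that the stated rule produces false flags two and a half times too often; the documents support this only as one conditional case, within a range from no inflation (Bonferroni) to 2.4 times.

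Second, Shapiro-Wilk is named in the same sentence, and Wilcoxon may be a garbled way of naming the non-parametric alternative. This also stands in part. A reader might infer that skewed data would slip through to a t test, but Shapiro-Wilk would catch it, and nothing in the text lets a non-significant Wilcoxon overrule it. On the charitable reading only a wording fault remains, although Wilcoxon would still be a two-sample test where three arms call for Kruskal-Wallis.

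Two further inferences go too far. On normal data, Wilcoxon is significant in 39% or 77% of cases when the arms differ by 0.5 or 0.8 SD, but randomisation rules out such true shifts at baseline, which is assessed before the physiotherapy sessions start. Compounding 12.4% (a smaller simulation's figure for three pairs) over 13 baseline scores gives 1 − (1 − 0.124)^13 = 82%. That assumes independence, while the scores include four KOOS subscales and an anxiety item taken from the EuroQoL that is also counted. Even a single 5% test per score would give 1 − 0.95^13 = 49% on the same assumption, so much of that total comes from the number of variables.

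The reply does not remove the misfit between a t test and three arms, or the use of the result to choose the main model.

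**Conclusion.** The point holds in limited form. As written, the baseline method does not suit three arms, and Wilcoxon does not belong among the distribution checks. If the t tests are run unadjusted at two-sided 5% with 25 per arm, a false baseline difference arises in about 9% to 12% of trials per variable, against 5% for one three-group test, and that flag moves the main analysis from repeated-measures ANOVA to ANCOVA. The size depends on the assumed pairs and on the absence of adjustment, neither of which is stated. No effect on the sample size follows, and no bias in a treatment estimate has been shown. This is a minor-to-moderate correction, worth making because the sentence feeds the choice of main model.

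**What to change.** Delete Wilcoxon as a distribution check and replace the baseline and ANCOVA sentences together, for example:

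> Baseline characteristics will be summarised by arm (mean and SD, or median and quartiles when skewed) without significance tests. Each outcome will be analysed with adjustment for its baseline score, whatever the baseline summaries show.

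The second sentence is needed. Deleting the baseline test alone would leave the ANCOVA rule without a trigger. Substituting a three-group test alone would lower the false-flag rate but keep the data-driven switch.

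If the team still wants a baseline test for description, it should be one three-group test per variable: one-way ANOVA, or Kruskal-Wallis when residual plots or Shapiro-Wilk indicate non-normality. It should have no bearing on the choice of outcome model.

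The cost is the rewording of two sentences, with no extra data and no extra participants.
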